## Resources

|                                                                                                                                                                                                                                                                                                                                                                                                                                                                                                                                                                                                                                                                                                                                                                                                                                                                                                                                                                                                                                                                                                                                                                                                                                                                                                                                           |
|-------------------------------------------------------------------------------------------------------------------------------------------------------------------------------------------------------------------------------------------------------------------------------------------------------------------------------------------------------------------------------------------------------------------------------------------------------------------------------------------------------------------------------------------------------------------------------------------------------------------------------------------------------------------------------------------------------------------------------------------------------------------------------------------------------------------------------------------------------------------------------------------------------------------------------------------------------------------------------------------------------------------------------------------------------------------------------------------------------------------------------------------------------------------------------------------------------------------------------------------------------------------------------------------------------------------------------------------|
| 
What resources are necessary for the project to be conducted?
 
These resource types will need to be taken into consideration including the funding to support the project, the clinics or community aged care centres to provide participations, human resources (the research team) to conduct the project, material resources and supplies (software for data analysis, cabin to store the documents, etc), the coordination and cooperation with other institutes
 
This study is funded by the Australian Government via 2020 Medical Research Future Fund (MRFF) 2020 Dementia Ageing and Aged Care Mission and 2020 NHMRC/DCRC World Class Research Project Grants. The funding will assist [name] to work as a full-time PhD student and other personnel to work in the project to achieve the study objectives. The project is fully supported by four industry partners including Southern Adelaide Local Health Network (SALHN; led by [name] and [name]), Canberra Health Services (led by [name]), Bolton Clarke Victoria (led by [name]) and Resthaven SA (led by [name]) via their signed agreements on the 2020 Medical Research Future Fund (MRFF) and 2020 NHMRC/DCRC World Class Research Project Grants (available on the request). The
 |
|-------------------------------------------------------------------------------------------------------------------------------------------------------------------------------------------------------------------------------------------------------------------------------------------------------------------------------------------------------------------------------------------------------------------------------------------------------------------------------------------------------------------------------------------------------------------------------------------------------------------------------------------------------------------------------------------------------------------------------------------------------------------------------------------------------------------------------------------------------------------------------------------------------------------------------------------------------------------------------------------------------------------------------------------------------------------------------------------------------------------------------------------------------------------------------------------------------------------------------------------------------------------------------------------------------------------------------------------|

project team possesses expertise, resources and collaboration with industry partners to implement research activities described in this study protocol.

**Please declare what funding support and amount is being sought or has been secured for this project:**

This study is part of large project funded by the Australian Government via 2020 Medical Research Future Fund (MRFF) 2020 Dementia Ageing and Aged Care Mission (\$1,406,658) and 2020 NHMRC/DCRC World Class Research Project Grants (\$536,586).

## Project design

Please refer to the [National Statement Chapter 3.1 Elements of Research](#) for guidance on to how to ensure this research is conducted in line with core ethical principles.

**Introduction** – Please provide a brief overview of the study:

This study is part of a large health service research project: “Creating ‘Partnership in iSupport program’ to optimise carers’ impact on dementia care”. The ‘Partnership in iSupport program’ includes (1) a program facilitator who acts as a link worker to assist informal carers (family, friends and neighbours) to navigate, access and utilise dementia care services; (2) psychoeducation for informal carers to improve their dementia care capabilities; and (3) virtual carer support groups to strengthen social support for informal carers (we use the word ‘carers’ onwards in the protocol). The aims of the project are to (1) co-design activities delivered by iSupport Program facilitators (Phase 1); (2) determine the intervention efficacy and cost-effectiveness (Phase 2); and (3) translate the program into practice (Phase 3). In this application, we seek ethics approval for Phase 2: determine the intervention efficacy and cost-effectiveness of the ‘Partnership in iSupport program’.

The overall aim of this study is to improve quality of life for people living with dementia (PLWD) and their carers by creating an innovative patient-centred approach, ‘Partnership in iSupport program’, which supports holistic and multidisciplinary care for PLWD.

**Background and literature review**

In Australia, 200,000 informal carers provide care for PLWD in the community (Alzheimer's Australia, 2015). They are the cornerstone of helping PLWD remain at home for as long as possible (Cheng et al., 2020). However, they have received less education preparation and limited ongoing support than professional carers to manage

dementia and other complex health issues for PLWD (Bressan, Visintini, & Palese, 2020). Care services for the PLWD after diagnosis are highly fragmented and difficult for carers to navigate and utilise (Steiner et al., 2020). Carers feel socially isolated due to time spent on care, stigma and the lack of quality social networks (Greenwood, Mezey, & Smith, 2018). Caregiver stress and distress are widely reported and contribute to poor health and quality of life (QoL) of both carers and PLWD and to the premature permanent admission to nursing home care of PLWD (Cepoiu-Martin, Tam-Tham, Patten, Maxwell, & Hogan, 2016; Stall et al., 2019). A recent study in the USA, using the National Inpatient Sample from 2012 to 2016, revealed that 40% of hospitalisations of PLWD were due to potentially preventable conditions, for example falls, injuries, dehydration, poisoning or uncontrolled chronic diseases (Anderson, Marcantonio, McCarthy, & Herzig, 2020) strongly suggesting that educating and supporting carers to manage dementia and disease progression can avoid emergency department uses and hospital admissions.

We propose a 'Partnership in iSupport program' built on collaboration between dementia care service providers and informal carers of PLWD in hospital and community aged care settings to tackle the current problems. The intervention comprises (1) having a program facilitator appointed by the participating hospitals or the community aged care providers to act as link workers to assist carers to navigate, access and utilise care services to meet the holistic care needs of the PLWD; (2) a psychoeducation program for carers to improve their knowledge and skills in managing dementia using the online Australian iSupport for Dementia; and (3) virtual carer support groups to enhance socialisation and reduce social isolation for carers. Having a link worker who acts as a single point of contact for carers for a minimum of one-year post-diagnosis support is a standard care service in Scotland (Alzheimer Scotland, 2019). This kind of support is viewed as an innovative dementia care model in a research paper submitted to the 2018-2020 Royal Commission into Aged Care Quality and Safety (Dyer et al., 2019). Combining the three components in a program reflects the stakeholders' expectations for providing a one-stop-shop for PLWD after diagnosis in a recent Australia study (Steiner et al., 2020). The program will use digital technology to improve reach to carers.

We have strong evidence through a systematic review by Cheng et al. (2020) that these three intervention components can significantly improve positive thoughts, subjective wellbeing, ability to manage dementia, social support, reduce mental health problems and stress for carers. The review has also confirmed that multicomponent intervention has the largest effects, compared to an intervention with a single component (Cheng et

al., 2020). This is health service research and our strong support from four partner organisations, Resthaven, Bolton Clarke Victoria, Southern Adelaide Local Health Network (SALHN) and Canberra Health Services is critical to this project success. CIA [name] has recently led a pilot study with 25 carers in collaboration with Resthaven to test the feasibility of this study and has confirmed that the intervention design was widely acceptable by both carers and the care service provider ([name], 2020).

**A link worker and potential impact:** Two recent systematic reviews have confirmed that having a link worker to assist carers to navigate, access and utilise dementia care resources and multidisciplinary care services can significantly improve carers' QoL and reduce their stress (Cheng et al., 2020; Goeman, Renehan, & Koch, 2016). A link worker is essential to bridge care gaps and prevent care crises during transitions between care settings and types (Alzheimer Scotland, 2019).

**Psychoeducation and potential impact:** Systematic reviews have determined that psychoeducation programs can significantly improve carers' QoL, self-efficacy and reduced stress (Cheng et al., 2020; Frias et al., 2020). The Australian iSupport program is a well-designed psychoeducation program for informal carers and is adapted from a generic version of the World Health Organization (WHO) iSupport for Dementia led by CIA [name] ([name] et al., 2020). iSupport embeds holistic care, for example, providing opportunities for PLWD to choose and control activities which are meaningful, enjoyable, and relevant to their life experience. iSupport uses techniques such as cognitive behavioural therapy to help carers develop positive thoughts, problem-solving and coping skills, self-care, and assertiveness when seeking help from relatives, friends and formal care service providers. The program covers dementia care from early stage to the end of life. Therefore, it helps carers learn about changes as dementia progresses and take proactive action to gain timely treatment and care. When appropriate, the program introduces dementia care resources and multidisciplinary care services with weblinks for carers to access. The Australian iSupport program currently contains 6 modules and 30 units: introduction to dementia; being a carer; caring for me; providing everyday care; and a person-centred care approach to changed behaviour and my engagement in consumer directed care.

**Virtual carer support groups and potential impact:** The systematic review by Cheng et al. has confirmed that carer support groups can significantly reduce stress and improve self-efficacy and QoL for carers (Cheng et al., 2020). Video-streaming meetings facilitated by trained health professionals demonstrates better health

outcomes for carers (Etxeberria, Salaberria, & Gorostiaga). Virtual support groups enable carers to share their knowledge, experiences in dementia care, to learn from role models and to help each other (Etxeberria et al.). Working carers particularly welcome virtual carer support as they can choose a time to participate.

#### **Creating reciprocal partnerships to support patient-centred approach:**

As detailed in the project methodology, iSupport program facilitators appointed by care service providers will assist carers to identify the individualised care needs of PLWD in a timely manner, especially when the PLWD's health condition is deteriorating or during the transitions between care settings (i.e., hospital-to-home) and care types (i.e., receiving palliative care at home). The facilitator will also assist carers to access and utilise relevant care services and co-plan care activities with carers and PLWD. It is anticipated that these supports will meet the care needs and improve QoL of PLWD, prevent and manage behavioural and psychological symptoms of dementia (BPSD) and complications; thus, reduce preventable conditions that contribute to emergency department uses and hospitalisations of PLWD. Further, the carer support group activities facilitated by the facilitator in the study will create opportunities and empower carers to provide constructive feedback to care service providers regarding the strengths and weaknesses of service. Their feedback will benefit the continuous quality improvement, organisational development, and staff development for the care service providers. Poor quality of care was identified by the 2018-2020 Royal Commission into Aged Care Quality and Safety as a significant issue. Only 20% of people receiving home care package felt their care needs were always met across all quality-of-care attributes ([name] et al., 2020). The reciprocal partnerships built through the program will have high potential to mitigate the issues.

#### **Hypothesis**

**Primary hypotheses:** Compared to those allocated to the usual care group, (1) carers receiving the intervention will report (a) at least a 5-point higher mean score on the mental component of the 12-Item Short-Form Health Survey (SF-12) and (b) an improved mean score on the physical component of SF-12; (2) their care recipients will report an improved mean score on the QoL in Alzheimer's Disease (QOL-AD)-Proxy at 12-months follow-up.

**Secondary hypotheses:** Compared to those allocated to the usual care group, (1) carers in the intervention group will report (a) an improved mean score on the Caregiving Self-Efficacy Scale and (b) an improved mean score on the Quality of Social Support

Scale; (2) their care recipients will report (carers acting as proxy respondents) (a) a reduced mean score on the Revised Memory and Behaviour Problem Checklist and (b) fewer unplanned hospital admissions, less emergency department uses and less use of permanent residential aged care at 12 months; and (3) provision of the intervention will be more cost-effective than existing care.

**Aims** - (1) **Aim 1:** to determine the intervention efficacy; (2) **Aim 2:** to establish the intervention cost-effectiveness; and (3) **Aim 3:** to understand carers' experiences in the program.

**Objectives** - How will investigators achieve the aims of the research project?

**Objective 1:** A multicentre randomised controlled trial (RCT) with carers of PLWD will be conducted to test the primary and secondary hypotheses or the intervention efficacy (Aim 1). The intervention will last 12 months.

**Objective 2:** The cost effectiveness analysis will be undertaken alongside the RCT (Aim 2). The primary outcome will be the incremental cost per quality adjusted life years (QALYs) gained for the intervention compared to usual care.

**Objective 3:** A qualitative descriptive design described by Doyle et al. (2019) will be applied to understand carers' experiences in the program (Aim 3) using data from the virtual carer support group meetings.

**Expected outcomes** - What do the investigators anticipate the outcomes of this research will be?

1. The expected outcomes for carers include improved quality of life (QoL), improved self-efficacy, improved quality of social support and positive learning experience in the program.
2. The expected outcomes for the persons with dementia include improved quality of life (rated by carers) and reduced memory and behaviour problem (rated by carers).
3. Improved quality adjusted life years (QALYs) from the perspective of carers and people with dementia compared to usual care.

#### **Rationale / justification**

In Australia, 200,000 informal carers provide care for people with dementia in the community and more than half of them are of working age (Alzheimer's Australia, 2015). They are the cornerstone of helping people with dementia remain at home for as long as possible (Alzheimer's Australia, 2015). They also play a crucial role in preventing dementia associated complications, reducing hospitalisation rates for this population and mediating treatment interventions led by health professionals (Bott et

al., 2019). However, they are less prepared to take on their role than professional carers (Bott et al., 2019; [name] et al., 2020). Better preparing this large carer cohort through education and peer support requires innovative models of program delivery with strong support from various dementia care service providers. Online education and virtual social support for carers demonstrate efficacy and increase reach to carers (Egan et al., 2018; Etxeberria et al.; Oliver et al., 2017). Dementia care service providers need to involve carers in dementia education to strengthen partnerships with them. The partnership can be critical for achieving person-centred care and effective treatment interventions for people with dementia (Bott et al., 2019; [name] et al., 2020). We have gained strong support from four industry partners, Southern Adelaide Local Health Network (SALHN), Canberra Health Services, Bolton Clarke Victoria and Resthaven SA, to implement and evaluate the Australian iSupport program in community aged care and hospital memory and geriatric clinics, aged care and dementia care wards, and ambulatory geriatric services, generating rigorous evidence to inform dementia care policy and practice development.

### **Research project setting**

The participants of the study are informal carers of PLWD in home care settings. The interventions will be delivered by four participating organisations in the study including SALHN, Canberra Health Services, Resthaven SA and Bolton Clarke Victoria.

### **Methodological approach**

#### ***Study Design***

A multicentre RCT with carers of PLWD will be conducted to test the primary and secondary hypotheses. The intervention will last 12 months. The cost effectiveness analysis will be undertaken alongside the RCT. A qualitative descriptive design will be applied to explore carers' experience in the program using data from the virtual carer support group meetings. The across-method triangulation used in the study via a combination of an RCT and a qualitative strand will facilitate a more holistic understanding of iSupport implementation (Denzin, 2017).

#### ***Settings and participants***

Participants will be informal carers (family, friends and neighbours) of people living with dementia (PLWD) who live at home. They will be recruited through various care settings as described in the following:

#### **(1) SALHN and Canberra Health Services:**

The study will be conducted in various care settings managed by SALHN and

Canberra Health Services, for example in the memory and geriatric clinics, ambulatory geriatric services and falls clinics for community dwelling PLWD, aged care and dementia care wards where PLWD are ready to be discharged home and are expected to live at home for at least 12 months.

**(2) Resthaven SA and Bolton Clarke Victoria:**

The study will be conducted in community aged care settings where PLWD receive home care package and have informal carers to support them at home.

***Randomisation and interventions***

After baseline data collection, carers will be randomly assigned to receive either the iSupport program or the usual care. To ensure the two groups are of equivalent size and conditions, a block randomisation will be used to allocate carers to one of the two treatment groups for each recruitment site. Stratification will also be used in the block randomisation to ensure equivalent distribution of spouse carers versus non-spouse carers and care recipients with mild versus moderate dementia in each treatment group.

**Arm 1–Usual care group:** Carers will receive the usual carer support provided by Dementia Australia or other publicly funded carer support. They will receive a monthly reminder email that directs them to the Dementia Australia website where they can seek support if they wish.

**Arm 2–Intervention group:** The planned interventions are described in the following.

- (1) Managing transitions: In each study site, carers will be assigned to an iSupport program facilitator and encouraged to request individualised support from the facilitator during transition between care settings (i.e. from hospital to home transitional care) and types (i.e. receiving ambulatory geriatric services, or rehabilitation or palliative care at home in addition to usual home care package) of the PLWD.
- (2) Managing dementia progression: Carers are also encouraged to contact the facilitator to discuss changes in PLWD (i.e., signs of deterioration, changed behaviours and complications) and gain advice to access relevant multidisciplinary care services for timely treatment and care. The facilitator will follow the carers until their needs for support have been met.
- (3) Psychoeducation: Carers will select at least 20 out of 30 learning units that are relevant to them from the online iSupport program to learn over the first 6 months of the trial and revisit or learn new units when they feel it is needed in the second 6 months. The expected time spent on learning the online iSupport learning modules

is no more than 12 hours in total. The completion of each unit will be measured through the program design and will be recorded as data for compliance with the intervention. Carers will receive a certificate for each unit they complete, a strategy to motivate them in the program.

- (4) Carer support group: In each study site, the facilitator will assign the 23 carers into one of two support groups. The facilitator will conduct a monthly online carer support group meeting lasting no more than 30 minutes. Managing transitions between care settings and types and managing disease progression will be standard meeting agenda so that carers can share their experiences and support each other in these dementia caregiving areas. The meetings will be recorded for carers in the same group to access. The facilitator will also create carer support groups in WhatsApp to encourage carers to talk or send text messages to their peers in the same group to strengthen social support. Text message or follow up phone calls will be used if carers cannot access WhatsApp or zoom (i.e., have no internet or smartphone). The facilitator will analyse group interactions, investigate carers' needs for support and provide feedback to them.
- (5) Feedback on services: The facilitators will collect carers' feedback via regular carer support meetings and discuss the feedback in their organisation's quality improvement meetings.
- (6) Confidentiality: Carers will follow an agreed protocol as described in the information sheet to maintain confidentiality and privacy in group activities.

**Consumer and Community engagement** – investigators are encouraged to consult with Consumer and Community groups with the design of their research. Please outline any consultation that has occurred.

**Governance and consumer engagement:** The research proposal has been reviewed by 4 carers and 3 staff nominated by industry partners in the study. Moreover, the interventions as described above have been discussed with stakeholders (carers and staff who provide care for people with dementia) in Phase 1 prior to this study phase. Their feedback has been addressed to ensure their voice in this study is heard from the outset. A Steering Committee will be established to govern the study. The committee members will include the project team. The committee will oversee all processes and outcomes of the study and will meet monthly video meetings to ensure the rigor of the study is maintained. A PhD student, [name] will be located at Flinders University to coordinate the project across all sites, assist consultations with stakeholders, update the project website and report findings. A Co-design Advisory Group will include 5 carers and 5 professional dementia care experts to ensure

consumer involvement. The researcher, [name], will coordinate activities with members of the Co-design Advisory Group. The project team will meet quarterly with the Advisory Group via online meetings to foster the co-design of iSupport implementation strategies.

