**Accounting for potential bias, confounding factors and missing information:**

[name] who does not involve in participants recruitment will randomly assign participants (deidentified) into the intervention group and usual care group. This approach will account for potential bias.

Confounding factors will be controlled through statistical analysis design. In order to control the interference of the confounding factors on the research results and reduce the potential bias, univariate models will be first used, then multivariate modelling will be undertaken by adding variables considered clinically important or statistically significant from the univariate model to adjust for confounding effects between variables. A series of models will be undertaken by adding and subtracting variables, with changes in model fit assessed by log likelihood to choose the final multivariate model.

Data will be analysed on an intention-to-treat basis based on group assignments. For missing information in the data analysis, Mean/Model Imputation will be used to reduce the bias in missing data completely at random.

**Sample size and statistical or power issues** – Make sure the size and profile of the sample to be recruited is adequate to answer the research question – please provide details:

The sample size calculation is based on the primary outcome of the SF-12 mental component for carers and is estimated on the basis of an earlier RCT with similar intervention components for carers (Berwig et al., 2017). In that study, the SF-12 mental component for carers increased significantly by an effect size of 0.57 and standard deviation of 8.63. We assume that the same effect size would be observed in our trial. The estimated sample size would be 66 carers per arm using a 2-sample comparison of means for  $\alpha=0.05$  at 90% of power. The Welch-Satterthwaite t-test is used to calculate the sample size for unequal variances. Assuming an attrition rate of 40%, the estimated sample size would be 184 carers in total or 92 per group. A stata code power was used to calculate the sample size. Our investigation indicates that each industry partner provides care services for more than 500 persons with dementia annually and more than 80% of carers use email to communicate with care staff which will ensure sufficient numbers of carers recruited into the study.

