**How will you measure, manipulate and/or analyse the information collected?**

**Measuring the effectiveness of the iSupport program:**

A research assistant, who will be blinded to group assignments, will undertake data analysis and will be supervised by CI [name], a biostatistician. Data will be analysed on an intention-to-treat basis based on group assignments. Descriptive statistics will be applied to summarise data. Binary correlation analysis will be performed to compare group using baseline data. A multivariate mixed effect linear regression model will be

applied to fit linear mixed models to examine the primary and secondary outcomes between groups. As the outcome occurs for each individual with repeated time points, the mixed effect models will capture both fixed effects and random effects within the hierarchical structure of the data. The fixed effects, including group effect, time effect and group x time interaction, will be analogous to the regression coefficients. The random effects represent the estimated variability in the intercept to account for repeated measurements. The model will be adjusted by the baseline measure of outcome variable. The maximum likelihood estimate procedure will be used to compare significant differences in primary and secondary outcomes over time and between groups. Univariate models will be first used, then multivariate modelling will be undertaken by adding variables considered clinically important or statistically significant from the univariate model to adjust for confounding effects between variables. A series of models will be undertaken by adding and subtracting variables, with changes in model fit assessed by log likelihood to choose the final multivariate model. The two-sided test will be performed for all analyses and the level of significance will be set at  $p < 0.05$ . All analyses will be performed using Stata software version 16.1.

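### Intervention carers are treated in eight support groups, but the sample size and mixed model assume independent carers; if outcomes correlate within groups, the standard error is too small and power is overstated

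*Protocol*

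**What the plan says.** **Delivery.** Protocol, Randomisation and interventions, item (4): "In each study site, the facilitator will assign the 23 carers into one of two support groups". The same item provides monthly online meetings and a WhatsApp group through which members are meant to support one another. Item (1) assigns the carers at each site to a program facilitator. The section on participant numbers plans four sites with 23 carers per arm at each. Usual care has no groups and no facilitator, only existing carer support and a monthly reminder email.

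**Analysis.** Protocol, Measuring the effectiveness of the iSupport program: the fixed effects are group, time and their interaction, with adjustment for the baseline value. On the random part it says: "The random effects represent the estimated variability in the intercept to account for repeated measurements". Estimation is by maximum likelihood.

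**Sample size.** Protocol, Sample size and statistical or power issues. The effect is borrowed from a previous trial of a similar intervention: "In that study, the SF-12 mental component for carers increased significantly by an effect size of 0.57 and standard deviation of 8.63". The resulting figure before dropout is given thus: "The estimated sample size would be 66 carers per arm using a 2-sample comparison of means". A Welch-type test that allows the two arms different variances is named as the method. Dropout is then allowed for: "Assuming an attrition rate of 40%, the estimated sample size would be 184 carers in total or 92 per group". No ICC or design effect appears.

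**The concern.** Carers in one support group share a facilitator, a year of meetings and a messaging group. Peer support is a named active component, so some similarity of outcome within a group is a foreseeable result of the intervention. Usual-care carers have no such structure, so any clustering sits in one arm only.

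The protocol does mention a hierarchical data structure, but ties it to repeated time points within an individual. The level above the carer is not modelled, and no cluster-robust variance is proposed. Because the protocol itself fixes the random-effects structure, this is a stated rule and not a detail left to a later analysis plan.

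At stake are confidence intervals that are too narrow and p-values that are too small, both in the direction that favours a positive finding, and a planned power that the design may not deliver.

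**Working it through.** **Inputs.** Standardised effect d = 0.57, two-sided alpha 0.05, power 90%, 66 per arm before attrition, 92 per arm enrolled, 40% attrition, four sites, two groups per site (all Protocol). Number of groups: 4 x 2 = 8. The ICC is not in the documents, so 0.01 to 0.10 is assumed.

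**Step 1: reproduce the plan's figure.** For d = 0.57 with independent carers, the normal approximation gives 65 per arm. The noncentral t gives power 0.897 at 65 and 0.902 at 66. The stated 66 therefore reproduces with a design effect of exactly 1, and no clustering allowance is hidden in it.

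**Step 2: add clustering in one arm.** Total variance is set to 1 in both arms. With n analysed per arm and m = n/8 per group:

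- intervention-arm design effect DE = 1 + (m - 1) x ICC
- true SE / naive SE = sqrt((DE + 1)/2)
- type I error of the naive test = 2 x (1 - Phi(1.96 / SE ratio))
- power (normal) = Phi(d / sqrt((DE + 1)/n) - 1.96)
- power (small df): noncentral t with Satterthwaite df, using 8 - 1 = 7 df for the intervention arm and n - 1 for usual care

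Example, n = 66, m = 8.25, ICC 0.05: DE = 1 + 7.25 x 0.05 = 1.36; SE ratio = sqrt(2.36/2) = 1.09; type I error = 2 x (1 - Phi(1.96/1.087)) = 7.1%; the df are 19.9.

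**66 analysed per arm (8.25 per group)**

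| Assumed ICC | DE | SE ratio | Type I error | Power, normal | Power, small df |
|---|---|---|---|---|---|
| 0.01 | 1.07 | 1.02 | 5.4% | 0.90 | 0.87 |
| 0.02 | 1.15 | 1.04 | 5.8% | 0.89 | 0.86 |
| 0.05 | 1.36 | 1.09 | 7.1% | 0.85 | 0.82 |
| 0.10 | 1.73 | 1.17 | 9.3% | 0.80 | 0.75 |

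A simulation of 20,000 trials with the naive Welch test gave type I errors of 4.9%, 7.4% and 9.4% at ICC 0, 0.05 and 0.10.

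**Step 3: repeat with the attrition the protocol assumes.** 92 x 0.6 = 55 per arm, or 6.9 per group.

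| Assumed ICC | Type I error | Power, normal | Power, small df |
|---|---|---|---|
| 0.01 | 5.3% | 0.84 | 0.81 |
| 0.02 | 5.7% | 0.83 | 0.79 |
| 0.05 | 6.7% | 0.80 | 0.76 |
| 0.10 | 8.5% | 0.75 | 0.70 |

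With 55 per arm, power is already 0.84 at ICC 0. That loss is not due to clustering. It arises because attrition was applied as 66 x 1.4 = 92.4 and not as 66/0.6 = 110, which is a separate error.

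**The case against.** **No correlation has been shown.** The documents give no ICC. At 0.01 to 0.02 the standard error changes by 2% to 4% and the type I error stays below 6%. Meetings take at most 12 x 30 minutes = 6 hours, against up to 12 hours of self-paced learning plus individual facilitator support, and carers without Zoom or WhatsApp are reached by text or phone. This stands as a limit on the size. It does not show that the ICC is zero, because WhatsApp contact is unmeasured and peer exchange is intended.

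**Under a strict null there is no inflation.** Randomisation is by individual carer. If the intervention changed nobody's outcome, shared groups would do nothing and the naive test would keep its level. This is right. The type I figures apply to a null of zero mean effect with group effects that vary around it.

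**Stronger readings.** A reader might infer that the standard errors are certainly too small; the documents support this only if the ICC exceeds zero. A reader might compute larger type I errors from 11.5 carers per group (6.2%, 8.1% and 11.3% at ICC 0.02, 0.05 and 0.10), but that is the enrolled group size with no attrition, while the protocol assumes 40%. A reader might also charge the whole fall from 90% power to clustering, although the step to 0.84 belongs to the attrition calculation.

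**The power figures leave out baseline adjustment**, which the protocol plans and which would raise power. This is fair. They are on the same unadjusted basis as the protocol's own calculation.

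**Conclusion.** The point holds in conditional form. The design creates a level of clustering in one arm that neither the model nor the sample size recognises, and nothing elsewhere in the protocol deals with it. That omission is certain; its consequence depends on an ICC the documents do not supply.

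With 66 analysed per arm, the effect is slight at an ICC of 0.01 to 0.02 and material at 0.05 to 0.10, where the naive standard error is about 8% to 14% too small (1 - 1/1.087 and 1 - 1/1.167). These results assume eight groups of equal size, equal total variance in both arms and no gain from baseline adjustment. The small-df power takes only seven df for the intervention arm, so part of its shortfall from 0.90 is the price of having few groups and not of the ICC itself.

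This should be corrected, but it does not by itself invalidate the trial.

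**What to change.** - **Model.** In Measuring the effectiveness of the iSupport program, add a support-group random effect that applies to the intervention arm only, with each usual-care carer as a singleton. Include site as a fixed effect, since randomisation is blocked by site. Fit by REML with Kenward-Roger or Satterthwaite degrees of freedom in place of maximum likelihood, because there are only eight groups.
- **Data.** Record each intervention carer's support group in the analysis file. The Matching section provides codes for participants and sites but mentions none for support groups.
- **Sample size.** Restate power over an assumed ICC range instead of enrolling more. For scale, 90% power with eight groups (normal approximation) would need 68, 70, 80 or 104 analysed per arm at ICC 0.01, 0.02, 0.05 or 0.10, against 65 at ICC 0. Correct the attrition inflation as a separate matter.
- **Stated limit.** The text implies one facilitator per site running both groups. A facilitator effect then cannot be separated from a site-by-treatment effect, and neither the group term nor the site fixed effect fully captures it. The plan should say so.

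**Cost.** One recorded variable and revised wording, wider intervals and a lower stated power. Group codes exist only in the intervention arm and would reveal allocation to the blinded analyst, so the plan needs a rule for this, such as having someone else run the final fit or releasing the codes only after the model is fixed.
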